## Abstract

Premenstrual syndrome (PMS) is a widespread and under-recognized disorder, characterized by cyclical recurrence of physical, psychological, and behavioral symptoms during the luteal phase, significantly impacting the daily functioning of women. Cognitive Behavioral Therapy (CBT) is an established non-pharmacological strategy for PMS, while *Brahmi* (Bacopa monnieri), a classical Ayurvedic herb, has traditionally been used to enhance cognition, reduce anxiety, and support emotional balance. This exploratory study evaluates whether combining *Brahmi* with CBT offers additional benefit compared to CBT alone. It is a double-blind, randomized, placebo-controlled exploratory clinical trial (CTRI/2025/02/081239) conducted at the Amrita School of Ayurveda, Kollam, Kerala, with sponsorship from the Central Council for Research in Ayurveda Sciences (CCRAS). Forty-six women aged 18–24 years, diagnosed with moderate to severe PMS using the Premenstrual Symptoms Screening Tool (PSST) and the Daily Record of Severity of Problems (DRSP), will be recruited and randomly assigned to receive either CBT with *Brahmi* tablets or CBT with placebo tablets. The primary outcomes include reduction in PMS severity, assessed by DRSP, and improvement in quality of life measured with the Quality of Life Enjoyment and Satisfaction Questionnaire (Q-LES-Q SF). Secondary outcome is reduction in functional disability measured using the Sheehan Disability Scale. Assessments will be conducted at baseline, during treatment, and at follow-up. Statistical analysis will be carried out using repeated measures ANOVA with Bonferroni-adjusted post hoc tests, significance set at *p* < 0.05, and effect sizes reported. A limitation of this design is that it cannot disentangle the individual effects of *Brahmi* from CBT, allowing conclusions only on the combined intervention. The study aims to generate preliminary exploratory evidence for a safe, integrative, and accessible approach to PMS management in young women.

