#### 4.2.1 Participant timeline

Participants enrolled in the study will undergo a structured series of visits spanning multiple menstrual cycles. During the first visit, personal history, socio-demographic information, and detailed menstrual history will be recorded. Participants will also complete the Patient Health Questionnaire-9 (PHQ-9) to assess depressive symptoms and the Premenstrual Symptoms Screening Tool (PSST) to evaluate the presence and severity of PMS. Individuals who meet the criteria for moderate to severe PMS based on the PSST will be considered eligible for further participation. At this stage, informed consent will be obtained. During the second visit, which occurs on the 1st or 2nd day of the subsequent menstrual cycle, the screening process will begin. This is followed by an initial Google Meet session at the same phase of the following cycle to confirm ongoing eligibility and provide further study orientation. The third visit (baseline) will be on 1st to 2nd day of the participant’s menstrual cycle, during which assessments using the Daily Record of Severity of Problems (DRSP), Quality of Life Enjoyment and Satisfaction Questionnaire (Q-LES-Q), and Sheehan Disability Scale (SDS) will be conducted. The intervention begins at the fourth visit (aligned with the 1st to 2nd day of the second menstrual cycle), where participants will be randomly assigned to receive either Cognitive Behavioral Therapy (CBT) combined with *Brahmi* tablets (interventional group) or CBT with placebo tablets (comparator group). CBT sessions will be given on the 5*^th^*, 12*^th^*, 19*^th^* and 26*^th^* day for 2 menstrual cycles with total of eight sessions. A final Google Meet follow-up will be conducted during the 1st to 2nd day of the fifth menstrual cycle to assess outcomes and gather participant feedback.

The schedule of visit chart is mentioned in Table 1. It explains the follow-up visits across four menstrual cycles during the study.

**TABLE 1 T1:** Schedule of visit chart.

Activity/assessment	1^st^ visit (history taking, PSST assessment)	2^nd^ visit (start screening 1^st^ to 2^nd^ day menstrual cycle)	G Meet (1^st^ to 2^nd^ day of next menstrual cycle)	3^rd^ visit Baseline visit (1^st^ to 2^nd^ day of menstrual cycle)	4^th^ visit (1^st^ to 2^nd^ day of 2^nd^ menstrual cycle)	G Meet (1^st^ to 2^nd^ day of 5^th^ menstrual cycle)
Personal history, socio-demographic data, and menstrual history						

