### 4.7 Exploratory statistical analysis

Exploratory statistical analysis will primarily explore the potential impact of Cognitive Behavioral Therapy (CBT) combined with either *Brahmi* (Bacopa monnieri) tablets or placebo in participants with moderate to severe Premenstrual Syndrome (PMS). Outcome measures include the Daily Record of Severity of Problems (DRSP), Quality of Life Enjoyment and Satisfaction Questionnaire (Q-LES-Q), and Sheehan Disability Scale (SDS), assessed at three time points: baseline (third visit), during treatment (fourth visit), and post-treatment (fifth cycle follow-up). Analyses will be descriptive, focusing on effect size estimates and 95% confidence intervals to provide insights into the direction and magnitude of observed effects. P values will be presented descriptively without inferential claims, in line with the exploratory nature of the study. Where appropriate, repeated measures approaches such as ANOVA or mixed-effects models may be applied to summarize changes over time and between groups, with emphasis placed on effect size interpretation to generate preliminary signals for future confirmatory research.

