### 4.8 Additional analyses

Subgroup analyses may be undertaken to explore potential differential impacts of therapies based on baseline characteristics such as age, severity of PMS symptoms, menstrual cycle regularity, or baseline psychological distress. Adjusted analyses using multivariate models may also be conducted to account for potential confounders (e.g., BMI, diet, baseline stress levels, or prior PMS-related therapies). These will be explicitly categorized as exploratory and interpreted cautiously. Interaction effects between CBT and *Brahmi* will also be examined if the sample size permits. Exploratory analyses may include treatment adherence, participant satisfaction, and patterns in biopsychosocial variables.

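### All three outcomes are scored before randomisation, but the stated analysis never adjusts for that score, so the between-arm estimate is less precise than it need be

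*Protocol article*

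**What the plan says.** The Abstract is firm on method: "Statistical analysis will be carried out using repeated measures ANOVA with Bonferroni-adjusted post hoc tests". Section 4.7 is looser: "repeated measures approaches such as ANOVA or mixed-effects models may be applied to summarize changes over time and between groups". It describes the three scales as "assessed at three time points: baseline (third visit), during treatment (fourth visit), and post-treatment (fifth cycle follow-up"), so baseline is counted among the repeated assessments.

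Section 4.2.1 places the first of these before randomisation: "The third visit (baseline) will be on 1st to 2nd day of the participant’s menstrual cycle", with all three scales completed then. Random assignment comes at the next visit: "The intervention begins at the fourth visit (aligned with the 1st to 2nd day of the second menstrual cycle"). Section 4.6.3 adds that DRSP is kept daily through two cycles before treatment.

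The only adjusted analyses are the optional ones in section 4.8, meant to "account for potential confounders (e.g., BMI, diet, baseline stress levels, or prior PMS-related therapies"). The baseline DRSP, Q-LES-Q or SDS score is not among the examples, although PMS severity does appear in the same section as a possible subgroup factor. On what will be reported, section 4.7 says "Analyses will be descriptive, focusing on effect size estimates and 95% confidence intervals".

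**The concern.** In a repeated measures ANOVA with baseline as one of the response levels, the pre-treatment score is treated as an outcome and not as information about the participant. The natural between-arm quantity is then the difference in change from baseline. It is a valid estimate, but it subtracts the whole baseline value whatever the correlation with the final score, and so carries more noise than an analysis that lets the data set the weight.

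With about 18 completers per arm and randomisation that is blocked but not stratified (sections 3.1 and 4.3), a chance difference in baseline severity between the arms would be no surprise. Baseline adjustment handles this and, in large samples, is never less precise than either the change score or the final score alone. Since the stated product of the trial is effect sizes with confidence intervals, the lost precision falls on exactly what will be reported.

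**Working it through.** **Inputs from section 4.2.2.** Pooled variance 2.85 (SD 1.688), mean difference 1.83, two-sided 0.05, nominal power 90%, dropout 20%.

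**The plan's own figure.** n = 2 × 2.85 × (1.96 + 1.28)² / 1.83² = 59.84 / 3.349 = 17.87, so 18 per group. 18 / 0.8 = 22.5, so 23 per group and 46 in total. The stated size reproduces.

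**Standardised difference.** d = 1.83 / √2.85 = 1.08.

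**Assumptions.** Equal SD at each visit, equal correlation ρ between visits, 18 analysed per arm. ρ is not in the documents; 0.3, 0.5 and 0.7 are shown.

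**Standard errors in SD units.** The base is √(2/18) = 0.333.

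- Baseline-to-final change: 0.333 × √(2(1 − ρ))
- Final score adjusted for baseline (ANCOVA): 0.333 × √(1 − ρ²)
- Ratio of the two: √(2 / (1 + ρ))

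| ρ | SE, change | SE, ANCOVA | Ratio |
|---|---|---|---|
| 0.3 | 0.394 | 0.318 | 1.24 |
| 0.5 | 0.333 | 0.289 | 1.15 |
| 0.7 | 0.258 | 0.238 | 1.08 |

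**Power at d = 1.08.** Noncentral t for the two contrasts. For the 2-df group-by-time test, noncentral F with noncentrality (18/2) × (2/3) × d² / (1 − ρ), that is 10.1, 14.1 and 23.5, on 2 and 68 df.

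| ρ | Change contrast | 2-df group-by-time | ANCOVA |
|---|---|---|---|
| 0.3 | 76% | 80% | 91% |
| 0.5 | 88% | 92% | 95% |
| 0.7 | 98% | 99% | 99% |

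**A smaller true effect.** The plan's d is large, which compresses the gap at high power. At an assumed d of 0.6, the change contrast has 32%, 42% and 62% power and ANCOVA 45%, 52% and 69%.

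**Interval width.** At ρ = 0.5 the 95% half-width, in the units of the plan's 1.83, is 2.03 × 1.688 × 0.333 = 1.14 for the change contrast and 2.03 × 1.688 × 0.289 = 0.99 with adjustment. Section 4.2.2 does not tie 1.83 and 2.85 to a named scale, so these widths cannot be assigned to DRSP, Q-LES-Q or SDS. The ratios do not depend on the scale.

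**Timing of the fourth visit.** Section 4.7 counts this visit as during treatment. Section 4.2.1 has randomisation and the start of treatment at that same visit, and Table 2 has SDS and Q-LES-Q look back over the previous cycle. A score taken then could describe a cycle before treatment.

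**The case against.** The strongest reply is that section 4.7 is permissive. It says models may be used, allows mixed-effects models (as does section 4.9), and fixes neither a covariate set nor a treatment contrast. A mixed model with baseline as covariate, or with a common baseline mean across arms, would fit its wording and recover roughly the ANCOVA precision. The covariate list in section 4.8 is introduced as examples, and an analysis plan not shown may settle the matter. This stands in part: nothing in section 4.7 forbids the better analysis. But the Abstract names repeated measures ANOVA without qualification, section 4.7 counts baseline as a time point, and no part of the article points to baseline adjustment.

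It is also fair that power matters less where p values are only descriptive, and that the gain is small at high correlation. The same precision loss still widens the confidence intervals, which are the stated focus.

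Two stronger readings are tempting, and the documents do not support either:

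- **Dilution of the effect.** A reader might infer that the treatment effect will be shrunk by averaging in the baseline visit. That would happen only if the group main effect over all three visits were reported: 1.83 would become 1.83 × 2/3 = 1.22, with power of about 82%, 73% and 65% at the three correlations, even with the full effect at both later visits. If the fourth visit were also before treatment, it would be 1.83 × 1/3 = 0.61, with 25% power at ρ = 0.5. But sections 4.1 and 4.2 define the outcomes as changes and section 4.7 speaks of change over time, which points to the group-by-time comparison. That comparison is not diluted.
- **Regression to the mean.** A reader might infer that selecting women with high scores biases the comparison. Selection acts on both randomised arms alike, so it cancels in expectation from the between-arm difference. Only chance imbalance remains.

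**Conclusion.** The point holds as one of avoidable imprecision. The analysis as stated would give an unbiased between-arm estimate with a standard error about 24%, 15% or 8% larger than a baseline-adjusted one at correlations of 0.3, 0.5 or 0.7. At the plan's own effect size and 18 per arm that is a loss of about 15, 7 or 1 points of power against the change contrast, and less against the 2-df group-by-time test. These figures rest on an assumed correlation, equal variances and equal correlation between visits. The article does not say that the group main effect will be reported, so dilution is a possibility to rule out and not an error in the plan. The improvement is worth making because it uses data already being collected.

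**What to change.** In section 4.7 and the Abstract, state that each of DRSP, Q-LES-Q and SDS will be compared between arms on post-treatment scores, with arm and the same scale's pre-treatment score as covariate. This can be ANCOVA, or a mixed model with baseline as covariate or with a common baseline mean across arms. Name the adjusted between-arm difference at the fifth-cycle follow-up, with its 95% CI, as the main estimate, and say that a group main effect averaged over baseline will not be used as the treatment effect.

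For DRSP, say which pre-treatment score is the covariate, for example one derived from the two screening diary cycles. Reconcile sections 4.2.1 and 4.7 on the fourth visit, and use that score as a response only if it is taken after treatment has started.

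The cost is wording and one degree of freedom per model. No new data, visits or participants are needed.

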#### 3.3.1 Inclusion criteria

Participants aged 18–24 years will be included to align with international youth definition while ensuring safety, methodological homogeneity, and minimizing confounding factors (26, 27).Regular menstruation with a menstrual interval of 25–35 days over the past 6 months.Participants scoring below 10 on the Patient Health Questionnaire-9 (PHQ-9) will be included, thereby excluding moderate to severe depression and ensuring the selection of individuals with PMS-related mood symptoms only.Diagnosed with moderate to severe PMS through PSST, the diagnosis will be confirmed with screening by the Daily Record of Severity of Problem (DRSP) scale for 2 menstrual cycles.

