## 4 Outcome measures

### 4.1 Exploratory primary outcomes

• Changes in PMS symptom severity, as measured by the Daily Record of Severity of Problems (DRSP) across two intervention cycles.

• Changes in quality of life, as assessed by the Quality-of-Life Enjoyment and Satisfaction Questionnaire Short Form (Q-LES-Q SF 12) from baseline to post-intervention.

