#### 4.2.2 Sample size

The proposed study is a randomized controlled exploratory trial aimed at providing preliminary insights into the comparative outcomes of two independent groups. As formal power calculations are not mandatory for exploratory studies, a two-sample t-test formula for comparing means was applied primarily to provide a rational basis for determining a feasible sample size:

$$n=\frac{2\,s_{p}^{2}\,{\left[Z_{1-\alpha /2}+Z_{1-\beta }\right]}^{2}}{\mu_{d}^{2}}$$

This formula incorporates the pooled variance, the anticipated mean difference between groups, the significance level (α), and statistical power (1−β). Using estimates from published data, the pooled variance (sp^2^) was taken as 2.85, and the expected mean difference (μd) between groups as 1.83. For reference, a two-sided test with a significance level of 0.05 (Z = 1.96) and a nominal power of 90% (Z = 1.28) was considered. Substituting these values yielded a preliminary estimate of approximately 18 participants per group. Allowing for an anticipated dropout rate of 20%, the adjusted number was approximately 23 participants per group, resulting in a total sample size of 46.

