#### 4.6.3 Pre-intervention observation (screening phase)

During Cycle 1 and Cycle 2, participants will maintain the Daily Record of Severity of Problems (DRSP) daily from Day 1 to the end of the 2nd cycle using paper-pencil in English. A follow-up virtual visit will be conducted on Day 1 or 2 of the 2nd cycle to review progress and clarify doubts. All DRSP scores and notes from the follow-up will be recorded in Microsoft Excel.

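### The analysis section does not name the randomised contrast as the effect estimate, while the stated combined-effect target can be read only from within-arm change, which can include regression to the mean

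*Protocol article*

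**What the plan says.** **Selection.** Women must have moderate to severe PMS on the PSST, and section 3.3.1 adds that "the diagnosis will be confirmed with screening by the Daily Record of Severity of Problem (DRSP) scale for 2 menstrual cycles". No DRSP cut-off is given.

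**DRSP record.** Section 4.6.3 says that in Cycles 1 and 2 "participants will maintain the Daily Record of Severity of Problems (DRSP) daily from Day 1 to the end of the 2nd cycle". Section 4.6.4 continues the diary in Cycles 3 and 4, the intervention cycles.

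**Outcomes.** Section 4.1 defines both primary outcomes as changes: DRSP across the two intervention cycles, and Q-LES-Q "from baseline to post-intervention". Neither definition mentions the comparator.

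**Analysis.** Section 4.7 states that the analysis will "primarily explore the potential impact of Cognitive Behavioral Therapy (CBT) combined with either" Brahmi or placebo tablets. It adds that "repeated measures approaches such as ANOVA or mixed-effects models may be applied to summarize changes over time and between groups", stresses effect sizes and 95% confidence intervals, and treats p values as descriptive. The abstract is firmer: "Statistical analysis will be carried out using repeated measures ANOVA with Bonferroni-adjusted post hoc tests", at p < 0.05.

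**Intended conclusion.** The abstract and section 6 say that the results will speak only to the two treatments together, and section 3.6 says that the design will show their combined effect. By contrast, sections 1.6 and 2.1.1 and the Trial-versus-Control comparison in section 4.6.7 describe a between-arm question.

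**The concern.** The stated target and the design do not match. CBT is common to both arms, so the difference between them isolates the tablet. The joint effect of CBT plus Brahmi has no randomised comparator in this trial. An analyst who follows the combined-effect wording has only the before-after change in the Brahmi arm to work with.

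That change is a poor guide here. Women admitted because their scores were high tend to score lower on re-measurement even if nothing works. If the diary that admitted them is also the DRSP baseline, the fall goes straight into the change score. Placebo response and natural fluctuation add to it.

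The descriptive label in section 4.7 does not protect the reader. It covers every estimate, the between-arm difference included, and the effect sizes are still meant to supply signals for a later trial. Regression to the mean is not mentioned anywhere, including in the limitations. What is at stake is that a later trial is planned on an apparent improvement that includes change not caused by treatment.

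**Working it through.** **1. The plan's own figure.** Section 4.2.2 rests on a two-sample comparison: "a two-sided test with a significance level of 0.05 (Z = 1.96) and a nominal power of 90% (Z = 1.28) was considered", the pooled variance "was taken as 2.85, and the expected mean difference" as 1.83. Then 2 × 2.85 × (1.96 + 1.28)² / 1.83² = 17.87, so 18 per group. Next, 18 / 0.8 = 22.5, so 23 per group and 46 in total. The stated figures are reproduced, and nothing in this point changes them. The check below uses 18 (completers) and 23 (randomised) per arm.

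**2. Is the screening diary the baseline?** Two screening cycles (section 4.6.3) and two intervention cycles (sections 3.4 and 4.6.4) make four. Section 4.2.1 also counts four cycles, with the last contact on day 1 or 2 of the fifth. No separate baseline cycle is left. However, section 4.2.1 places a DRSP assessment at a third, baseline visit and starts the intervention at the fourth, while section 4.7 calls the fourth visit during treatment. The inference is therefore reasonable but is not stated.

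**3. Which contrast answers which question?** CBT + Brahmi minus CBT + placebo gives the effect of adding Brahmi. A time effect, or a before-after change within one arm, mixes CBT, tablet, placebo response, natural course and regression to the mean. The abstract does not say what the Bonferroni tests compare. With two groups and three time points, time is the natural target, although group comparisons at each visit are possible.

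**4. Size when there is no treatment effect.** Assumptions that are not in the documents: normal scores; the worst 25% or 50% of women admitted; cycle-to-cycle correlation r of 0.5 to 0.9; selection and baseline on the same score S, which is the mean of k screening cycles; and one later cycle as the outcome. Scale so that a single-cycle score has SD 1 in unselected women.

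- Variance of S: v = r + (1 − r)/k. Covariance of S with the later cycle: r.
- Expected fall: λ(v − r)/√v, where λ = φ(c)/p for admitted fraction p and standard normal cut-off c. λ is 1.271 for p = 0.25 and 0.798 for p = 0.50.
- k = 2, p = 0.25, r = 0.5: 1.271 × 0.25/√0.75 = 0.37.
- k = 2, p = 0.50, r = 0.9: 0.798 × 0.05/√0.95 = 0.04.
- k = 1, p = 0.25, r = 0.5: 1.271 × 0.5 = 0.64.
- k = 1, p = 0.50, r = 0.9: 0.798 × 0.1 = 0.08.

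The last two columns give the simulated share of arms with a nominally significant improvement (paired t-test, two-sided 0.05), for 18 / 23 women per arm. Chance alone would give 2.5% in that direction.

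| Admitted | r | Fall, two-cycle mean | Fall, one cycle | Significant, two-cycle mean | Significant, one cycle |
|---|---|---|---|---|---|
| 25% | 0.5 | 0.37 | 0.64 | 43% / 53% | 81% / 90% |
| 25% | 0.7 | 0.21 | 0.38 | 24% / 30% | 56% / 67% |
| 25% | 0.9 | 0.07 | 0.13 | 10% / 12% | 21% / 26% |
| 50% | 0.5 | 0.23 | 0.40 | 20% / 24% | 41% / 52% |
| 50% | 0.7 | 0.13 | 0.24 | 12% / 15% | 26% / 33% |
| 50% | 0.9 | 0.04 | 0.08 | 6% / 7% | 11% / 13% |

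The between-arm t-test on change rejected in about 5% of trials in every setting.

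**The case against.** The strongest reply is that the plan nowhere names within-arm change as its effect measure and specifies no paired test. The wording in section 4.7 is ordinary for a two-arm repeated-measures analysis, which would include group-by-time. The word either may simply list the arms. The hypothesis is added benefit over CBT alone, the first objective is CBT with versus without Brahmi, the sample size comes from a two-group comparison, and section 4.6.7 plans Trial versus Control. Section 4.7 disclaims inference, and sections 6 and 7 disclaim causal conclusions. The precise contrast is also something that an analysis plan often settles.

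Much of this stands. A reader might infer that the Brahmi-placebo comparison is biased. It is not, because both randomised arms regress equally on average. A reader might also infer that the plan has adopted before-after change as its effect measure. It has not; it lists such change beside the group difference and leaves the choice open.

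What the reply does not remove is the conflict inside the protocol. The combined-effect statements are made in this document, and no randomised contrast in the trial can deliver them. A later analysis plan cannot cure that while the stated target remains. The disclaimers limit the strength of claims, but they do not say which estimate is free of regression to the mean.

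**Conclusion.** The point holds as a mismatch between stated target and design, with a risk of misreading that follows from it. It is not an error in the randomised comparison.

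Its size cannot be fixed from the documents, which give neither a DRSP cut-off nor a cycle-to-cycle correlation. Under the assumptions above, the spurious within-arm fall is about 0.04 to 0.37 SD with a two-cycle mean baseline, which fits the diary schedule better, and about 0.08 to 0.64 SD with a one-cycle baseline. It would be tempting to say that both arms will probably show a clear fall. At a correlation of 0.9 with two-cycle averaging the fall is only 0.04 to 0.07 SD, so that claim is not supported across the range.

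Two limits apply. Use of the screening diary as DRSP baseline is inferred from the cycle count, because the visit labels conflict. Q-LES-Q and SDS are not selection tools, so they are affected only through their correlation with the PSST and DRSP.

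**What to change.** 1. In sections 4.1 and 4.7, name the between-arm difference (CBT + Brahmi minus CBT + placebo, as group-by-time or as follow-up adjusted for baseline, with 95% CI) as the estimate from which any signal is read. Bring the abstract's account of the analysis into line.
2. Show within-arm means over time as summaries only, and state that they include regression to the mean and are not attributable to treatment.
3. Reword the target in section 4.7 and the combined-effect statements in the abstract and sections 3.6 and 6 to the effect of adding Brahmi rather than placebo to CBT. Section 7 should follow.
4. Reconcile the visit labels in sections 4.2.1, 4.6 and 4.7, and state which cycle or cycles form the DRSP baseline.

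This is a change of wording. It needs no new data and leaves the 46 participants unchanged. The cost is that large within-arm improvements can no longer be presented as effects.
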